### Data analysis

In a stepped wedge study, the distribution of results across unexposed observation periods is compared with the distribution of results across the exposed observation periods [62]. The data in the present study will be analyzed using an Intention-to-treat approach and by a blinded statistician. In the BLEND-A study, the evaluation will be conducted over a 16-month period during which the proportion of clusters exposed to the blended treatment intervention gradually increases. Adjusting for the systematically different observation periods and for clustering in the data will be accomplished by fitting an appropriate generalized linear mixed model or using generalized estimating equations (GLMM). We may also decide to examine how the impact of implementing blended treatment develops (over time) once it is introduced into a cluster, since the intervention may need an initial period of adjustment before becoming fully embedded in the setting. Hence, the length of the period (up to the current observation) during which the cluster (treatment institution) has been exposed to the intervention may be included in the model as an effect modifier [62].

#### Economic analyses

The economic analysis includes 1) cost comparisons, 2) a cost and benefits comparison, 3) a formal cost-effectiveness incremental cost-effectiveness ratio (ICER: ratio of Net Costs to Net quality-adjusted life-years (QALYs)), and 4) a business case analysis. Cost comparisons entail cost estimation of either of the interventions (BLEND-A or TAU), including costs that are directly related to the interventions and costs associated with the impact of the interventions on patients, i.e. health care utilization, social care, patients’ own resources and labor supply/productivity. Data on the use of resources will be extracted from population registries maintained by Statistics Denmark and The Danish Health Data Authority, and will be supplemented with data from the municipalities’ own databases and ad hoc measurements (especially for resources directly related to the interventions). Net costs, ∆C = (Costs(BLEND-A) minus Costs(TAU)), will be assessed with means, medians, and statistical tests, and decomposed into health net costs and social net costs. Prices and wage rates will be based on negotiated/market prices, DRG-rates and similar. Sub-group analyses will be performed for different patient categories.

Costs and benefits (premature dropouts, decreased alcohol intake, and increased quality of life at 6 months after treatment intake) in the two intervention groups will be compared and described to assess cost-effectiveness. A formal cost-effectiveness analysis will be performed according to international standards [63–65]. Validity of the EQ-5D, being a generic Quality of life (QoL) instrument, will be empirically assessed in the study by comparing EQ-5D measures with patient reported outcome (PRO) data. ICERs and sensitivity analysis will be estimated with non-parametric bootstrap-based confidence intervals.

Finally, we aim to perform a business case calculation using the Danish framework so that the municipalities can perform their own business cases to assess the consequences of implementing BLEND-A.

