Mental health care institutions are increasingly introducing blended treatment, and an evidence base has emerged demonstrating the clinical and cost-effectiveness of this type of treatment for a number of psychiatric disorders [14, 29, 31, 35–39]. Studies on the development and implementation of blended treatment for substance use disorders are still scarce [40]. In the context of AUD treatment, no studies have, to our knowledge, compared the effects of blended and traditional face-to-face treatments on a larger scale. This is despite the fact that many AUD patients, particularly those with more severe AUD, may benefit from combining face-to-face sessions with internet modules within the same treatment protocol [7, 41–43], thereby still involving face-to-face contact and making treatment easier to complete. Notwithstanding, blended treatment targeting AUD is currently offered at the Jellinek outpatient institutions in the Netherlands. The Jellinek blended treatment protocol is highly structured and based on evidence-based psychological treatment consisting of MI and CBT [1, 3], and both the clinical and implementation experiences have been positive. Further, a pilot-study testing this treatment program in three outpatient institutions in Denmark has shown promising preliminary results [44]. Therefore, the present large-scale study, “BLEND-A: Blending internet treatment into conventional face-to-face treatment for AUD”, was designed and developed.

The central aim of the BLEND-A Study is to examine and evaluate the effectiveness of the blended treatment program in an implementation framework allowing a country-wide upscale of AUD-treatment reach. We hypothesize that:
BLEND-A (internet-based modules combined with face-to-face outpatient treatment within the same protocol) will lead to a 10-percentage point better treatment compliance (primary outcome), measured as decreased premature dropout from treatment (dropout from treatment before planned conclusion), compared to TAU (face-to face outpatient treatment).BLEND-A will be more effective in reducing alcohol consumption (secondary outcome), measured via self-report 6 months after treatment intake, compared to TAUBLEND-A will lead to better quality of life (secondary outcome) 6 months after treatment start compared to TAU.BLEND-A will be a cost-effective treatment approach, comparable to face-to-face treatment (secondary outcome).

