### Study design

The study is a pragmatic, stepped wedge cluster randomized controlled trial [46].

After implementation of the BLEND-A protocol in the participating treatment institutions, we expect that 25–40% of the consecutively enrolled patients will be offered blended treatment and accept to receive it. The decision of whether a patient will receive blended treatment will be made by the therapist and patient together during the first treatment session, taking into consideration the participant’s education, literacy, and computer skills.

Patients not receiving blended treatment are expected to continue receiving face-to-face treatment only. Up to 40 % of the patients are assumed to make use of the possibility of blended treatment. Thus, randomization to BLEND-A treatment and face-to-face treatment is not considered possible at the individual level due to the element of shared decision making in the blended care protocol. Instead, we will use a stepped wedge cluster randomized design [47] and randomize the treatment institutions to implement a new routine in which BLEND-A is offered to patients as a possible alternative to face-to-face treatment.

The BLEND-A study design is, thus, a pragmatic, stepped wedge cluster randomized controlled trial of a blended treatment alcohol intervention incorporating evaluations of the clinical effectiveness of the intervention, its economic impact, its perspectives for sustainable implementation in routine practice, and its impact on patient wellbeing and functioning.

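### The only stated measure of cost-effectiveness uncertainty is a bootstrap interval on the ICER, which cannot be interpreted if the QALY difference is not clearly away from zero

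*Protocol article*

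**What the plan says.** The Economic analyses section lists four components: cost comparisons, a comparison of costs and benefits, a formal ICER, and a business case. The formal result is defined as "ICER: ratio of Net Costs to Net quality-adjusted life-years (QALYs"), and its uncertainty is to be handled thus: "ICERs and sensitivity analysis will be estimated with non-parametric bootstrap-based confidence intervals". The section refers to international standards for the formal analysis. It does not mention net monetary benefit, a cost-effectiveness plane, an acceptability curve or a threshold.

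Two other statements determine how large the denominator can be. Under Study design, "we expect that 25–40% of the consecutively enrolled patients will be offered blended treatment and accept to receive it", and "Patients not receiving blended treatment are expected to continue receiving face-to-face treatment only". Under Data analysis, "The data in the present study will be analyzed using an Intention-to-treat approach and by a blinded statistician".

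The hypothesis served is the fourth in the Background: "BLEND-A will be a cost-effective treatment approach, comparable to face-to-face treatment". The third hypothesis in the same list predicts better quality of life than under usual treatment, without giving a size.

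**The concern.** A ratio jumps from minus to plus infinity (or the reverse) as its denominator passes through zero, and its sign does not identify the quadrant. A negative ICER means either cheaper and better or dearer and worse. A positive ICER means either dearer and better or cheaper and worse, and these call for opposite decision rules. Once bootstrap replicates of the QALY difference lie on both sides of zero, no ordering of the ratios corresponds to an ordering from favourable to unfavourable, so limits taken on the ratio do not bound anything a decision-maker can use.

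The contrast is between exposed and unexposed periods of an institution, and most patients in exposed periods are expected to stay on face-to-face treatment. The QALY difference in the denominator is therefore a diluted one. At stake is whether the formal cost-effectiveness result carries a usable statement of uncertainty.

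**Working it through.** **No plan figure to reproduce.** The article gives no QALY effect, no QALY SD, no ICC for QALYs and no power for quality of life. Its power statement (1800 patients, 31% versus 41% completion) concerns the primary outcome and does not bear on this point.

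**Step 1: why the ratio loses meaning.** Take an illustrative cost saving of 500 per user, a gain of 0.02 QALY per user and 25% uptake.
- Institution-level differences: ΔC = −500 × 0.25 = −125 and ΔE = 0.02 × 0.25 = 0.005. ICER = −125 / 0.005 = −25,000.
- Mirror-image replicate: ΔC = +125, ΔE = −0.005. ICER = 125 / (−0.005) = −25,000, the same value with the opposite meaning.
- Net monetary benefit, λ × ΔE − ΔC, at an illustrative λ = 200,000: 200,000 × 0.005 + 125 = +1,125 for the first and −1,125 for the second. The two are separated.

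**Step 2: dilution from the article's own uptake.** If non-users are unchanged, ΔE = uptake × per-user gain. The shrinkage is 1/0.40 = 2.5-fold to 1/0.25 = 4-fold.

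**Step 3: how often the QALY interval includes zero.**

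From the article: 18 institutions, four groups of movers after an unexposed period (so five periods), N = 1800, uptake 25–40%.

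Assumed: groups of 5/5/4/4, equal cells of 1800 / (18 × 5) = 20 patients, QALY SD 0.06–0.10 over 6 months, per-user gain 0.02–0.03, ICC 0.02, cluster autocorrelation 0.8.

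The variance comes from the Hussey-Hughes model with fixed period effects, extended by an institution-by-period effect. Variance components, as multiples of SD²:
- institution: 0.02 × 0.8 = 0.016
- institution-by-period: 0.02 × 0.2 = 0.004
- residual: 0.98

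Generalized least squares gives a standard error of about 0.079 × SD: 0.0047, 0.0063 and 0.0079 at SD 0.06, 0.08 and 0.10.

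With z = ΔE / SE, P(95% interval includes zero) = Φ(1.96 − z) − Φ(−1.96 − z).

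| Uptake, gain per user | ΔE | SD 0.06 | SD 0.08 | SD 0.10 |
|---|---|---|---|---|
| 25%, 0.02 | 0.0050 | 82% | 88% | 90% |
| 25%, 0.03 | 0.0075 | 65% | 78% | 84% |
| 40%, 0.02 | 0.0080 | 61% | 76% | 83% |
| 40%, 0.03 | 0.0120 | 28% | 52% | 67% |
| 40%, 0.05 | 0.0200 | 1% | 11% | 28% |

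Example: 25%, 0.02, SD 0.10 gives z = 0.005 / 0.0079 = 0.63 and Φ(1.33) − Φ(−2.59) = 0.90. The first four rows give the 28–90% range. The last row shows a larger gain largely escaping the problem.

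**Step 4: turned round.** Excluding a zero QALY difference with 80% power needs ΔE = (1.96 + 0.84) × SE. Per user that is 2.80 × 0.0047 / 0.40 = 0.033 at best and 2.80 × 0.0079 / 0.25 = 0.089 at worst within this range. Full EQ-5D data on 1800 patients is optimistic: EQ-5D comes from the study questionnaire, while the first step in the power calculation is prior-year register data, for which Table 1 lists no EQ-5D.

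**Step 5: effect on the interval.** A simpler simulation used no clustering, 900 per arm, QALY SD 0.15, cost SD 20,000, a saving of 500 per user and a threshold of 200,000, all assumed. At a gain of 0.02 and 25% uptake, percentile intervals on the ICER covered 100% instead of 95%, with a median width of about 2.9 million per QALY. With a gain of 0.05 and full uptake, coverage was 95% and the width about 78,000. Net-benefit intervals covered 94–97% throughout.

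**The case against.** The strongest reply is that the article is condensed. It promises a formal analysis to international standards, and net benefit, planes, acceptability curves and thresholds are ordinary content of a health-economic plan that is not shown. That stands as far as missing detail goes, and nothing in the article blocks those outputs. But the interval on the ratio is a specific stated choice, and an unseen plan that adds other outputs would not correct it.

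Four stronger readings are tempting, and the article does not support them.

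- *The interval will probably fail.* Low uptake scales an unknown effect; it does not by itself place that effect near zero. The plan hypothesizes better quality of life. It also expects a 10-point rise in completion across the institution, which at 40% uptake means 10 / 0.40 = 25 points among users if non-users are unchanged. The effect on users could be large.
- *The fourth hypothesis would get no answer, and municipalities an unusable figure.* Net costs are tested separately, costs and benefits are compared side by side, and municipalities are to receive a business case. None of these depends on the ratio interval, although none quantifies joint cost-effect uncertainty either.
- *The word comparable in that hypothesis means equal QALYs.* It is ambiguous, and it stands next to a prediction of better quality of life.
- *The bootstrap is the wrong tool, or a percentile interval is planned.* The resampling is sound, and the article does not say how the interval is constructed.

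The harm is also limited. In the low-gain simulation the interval was too wide rather than falsely narrow, and net benefit cannot make an imprecise QALY difference precise.

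**Conclusion.** The point holds as a conditional one. The article commits to a confidence interval on the ICER as its only named measure of joint uncertainty, and that interval is not interpretable if the bootstrap distribution of the QALY difference includes zero. The 2.5- to 4-fold dilution follows from the article's own uptake, provided non-users are unaffected. The 28–90% range rests wholly on the assumed SD, gain, ICC and autocorrelation. It shows that the problem is plausible, not that it is expected: with a gain of 0.05, 40% uptake and an SD of 0.06, it falls to about 1%. The primary outcome and the other economic components are not touched. Severity is minor to moderate.

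**What to change.** Make incremental net monetary benefit, with its confidence interval over a stated range of thresholds, the formal measure of uncertainty. Present it with the cost-effectiveness plane and an acceptability curve. All three come from the same bootstrap replicates, which should be drawn in a way that respects institutions and periods. Keep the ICER as a point estimate, and give an interval on it only when the QALY difference is clearly away from zero.

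The cost is a few sentences in the economic section or health-economic plan, with no new data. The small downside is that a threshold range must be named in advance and the headline is no longer a single ratio.

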#### Power calculations and number of participants needed in the study

In 2014, 31% of all patients seeking treatment at a publicly funded alcohol treatment institution completed the treatment pathway as planned [12, 66]. We hypothesize that implementing BLEND-A will lead to a 10-percentage point higher level of compliance compared to TAU, i.e. increasing the total number of patients who complete the treatment course at the treatment institution according to the NAB register.

We wish to be able to identify a 10-percentage point increase in overall treatment completion (from 31% now with treatment as usual to 41% with BLEND-A) with 80% power and a two-sided significance level of 5%. In order to secure the randomization process, we aim to involve at least two major institutions (enrolling more than 200 new patients per year, typically 300–600 patients), and additionally 6 or more minor treatment institutions (typically enrolling 60–80 new patients per year [66]). The power calculation, based on Hemming et al.’s recommendations for stepped wedge cluster randomized trials [47, 67], estimates that a total of 1800 individuals, enrolled in treatment at such 8 treatment centers and enrolled in four steps (the first two steps were 6 months apart, the others steps were 4.5 months apart) during a period of 20 months, will be sufficient to detect a 10 percentage point improvement with at least 80% power. Register data stemming from the year prior to the start of enrollment will be regarded as the first step. The figure below shows the power as a function of the improvement for various situations of intra-center-correlations, and the power is exceeded when the effect is a 10-percentage point improvement from 31 to 41% as specified.

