### Study procedure and randomization

All 61 publicly funded Danish treatment institutions were invited to participate in the effectiveness and implementation study. A total of 18 treatment institutions are included in the study. The included institutions are scattered all over the country, and the catchment areas cover approximately 30% of the Danish population.

The stepped wedge cluster randomized design includes an initial period in which no clusters are exposed to the intervention. Subsequently, at regular intervals of 3 months, one cluster or a group of clusters are randomized to cross from the control group to the intervention group. In the present study, the participating institutions were randomized into 1) first-movers, 2) second-movers, 3) third-movers, and 4) fourth-movers (see Fig. 1.).

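### The stated power and the sample size of 1800 are computed for a different design (8 centres, steps of 6 and 4.5 months, 20 months) from the one described (18 institutions, 3-month steps, 16 months)

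*Protocol article*

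**What the plan says.** The protocol article describes the design in two places that do not match.

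- **Power calculations and number of participants needed in the study.** The aim is to detect a rise in completion from 31% to 41% "with 80% power and a two-sided significance level of 5" per cent. The calculation rests on "a total of 1800 individuals, enrolled in treatment at such 8 treatment centers and enrolled in four steps", and on a calendar in which "the first two steps were 6 months apart, the others steps were 4.5 months apart) during a period of 20 months". It adds: "Register data stemming from the year prior to the start of enrollment will be regarded as the first step". The centres are to be at least two major ones (typically 300-600 new patients a year) and six or more minor ones (typically 60-80 a year).
- **Study procedure and randomization.** "A total of 18 treatment institutions are included in the study". They are randomised into four waves of movers, and "at regular intervals of 3 months, one cluster or a group of clusters are randomized to cross" to the intervention.
- **Data analysis.** "the evaluation will be conducted over a 16-month period".

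The abstract gives 1800 as the planned number of patients. ICC values appear only in a figure that is not available here.

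**The concern.** Power in a stepped-wedge trial depends on the number of clusters, the spacing of the crossings, the patients per cluster-period and the ICC. Three design features (centres, spacing, duration) differ between the power section and the rest of the article, while the sample size and the power claim are left unchanged. The claim has therefore not been shown for the trial that is described.

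A null result on the primary outcome will be read against this figure. If the true power for 1800 patients is nearer 60% than 80%, such a result says much less than the plan implies. If it is well above 80%, the plan understates what the trial can show.

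**Working it through.** **1. The two designs side by side**

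| Feature | Power section | Design and analysis sections |
|---|---|---|
| Centres | 8 | 18 |
| Step spacing | 6, then 4.5 months | 3 months |
| Duration | 20 months | 16 months |
| Planned number | 1800 | 1800 (abstract) |

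**2. Method.** Stepped-wedge generalised least squares on cluster-period means (Hussey-Hughes model), with fixed period effects and a random centre effect. Total variance is 0.36 × 0.64 = 0.2304, taking the mean of 31% and 41%. Power = Φ(0.10/SE − 1.96). The ICC is assumed over 0.001-0.10. Centres are of equal size unless stated.

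**3. The plan's own figure.** Periods are 12 months (register year), then 6, 4.5, 4.5 and 5 months, which makes 20 months of enrolment. With 1800 enrolled in 20 months, the register year adds 1800 × 12/20 = 1080.

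| ICC | 0.001 | 0.01 | 0.02 | 0.05 | 0.10 |
|---|---|---|---|---|---|
| Power, % | 91.5 | 85.9 | 84.9 | 84.9 | 86.4 |

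For example, at ICC 0.02 the SE is 0.0334 and Φ(0.10/0.0334 − 1.96) = Φ(1.03) = 0.85. The claim of at least 80% reproduces. With two major centres at 330 a year and six minor ones at 70 a year, average power over random allocations is 81-88%, and single allocations range from 71% to 93%.

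This reading of the register year fits the stated centre sizes. Enrolling 1800 in 20 months is 1080 a year, so with six minor centres at 70 each major centre enrols (1080 − 420)/2 = 330, inside the stated 300-600. If the 1800 spanned 32 months including the register year, the rate is 675 a year and each major centre enrols (675 − 420)/2 = 127.5, below the stated minimum of 200. Under that less plausible reading the power is 66-76%. If only three crossings are modelled, it is about 70-84%.

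**4. The described design with exactly 1800 patients.** There are 18 equal institutions in four waves (5, 5, 4, 4), 3-month steps and 16 months. With the register year as baseline, the periods are 12, 3, 3, 3 and 7 months. Without it they are 3, 3, 3, 3 and 4. The register year adds 1800 × 12/16 = 1350.

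| ICC | 0.001 | 0.01 | 0.02 | 0.05 | 0.10 |
|---|---|---|---|---|---|
| Register year added, % | 84.3 | 80.4 | 79.4 | 79.4 | 81.0 |
| No register year, % | 84.2 | 77.9 | 75.0 | 72.6 | 73.1 |
| Register year within the 1800, % | 61.7 | 58.1 | 56.8 | 56.3 | 57.7 |

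At ICC 0.02 with the register year added, the SE is 0.0360 and Φ(0.10/0.0360 − 1.96) = Φ(0.82) = 0.79. The difference detectable with 80% power is (1.96 + 0.84) × 0.0360 = 10.1 percentage points. With the register year inside the 1800, the SE is 0.0469 and the difference is 2.80 × 0.0469 = 13.1 points.

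Two sensitivities apply with the register year added. With two to four large centres, average power is about 76-81%. If 20% of the institution variance is step-specific, power with equal centres is about 79% at ICC 0.01 and 63% at ICC 0.10.

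**5. The described design at the stated enrolment rates.** The mix is assumed to be 2 major and 16 minor institutions, with the register year added and a constant ICC.

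| Major / minor, per year | Enrolled in 16 months | Average power, % |
|---|---|---|
| 300 / 60 | (600 + 960) × 16/12 = 2080 | 83-87 |
| 450 / 70 | (900 + 1120) × 16/12 = 2693 | 90-93 |

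At these rates power exceeds 80% on average, but enrolment exceeds 1800.

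**The case against.** Three points on the other side carry weight.

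- **The power section sets a minimum.** It asks for at least two major and six or more minor centres, so 18 institutions are allowed. This covers the centre count only. It does not reconcile 6- and 4.5-month steps with 3-month steps, or 20 months with 16.
- **The stated power is not an arithmetic error.** It reproduces on the section's own inputs with the register year on top. That is also the natural reading, since data from before enrolment are not part of those enrolled. The text does not say so outright, however, and the choice moves power for the described design by roughly 20 points.
- **The direction of the change is open.** The primary outcome comes from the national register for all patients at the institutions, so 18 of them may well yield more than 1800.

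A reader might infer that the trial is underpowered, or that the claim fails under most readings. The documents do not support either. With 1800 plus the register year the described design is borderline (79-84%), and at the stated rates it is above 80% on average. The lower figures need the register year left out or counted within the 1800, an ICC that decays over time, or large centres in unfavourable waves. None of these is stated in the plan.

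Nor is this a detail that an article leaves to a fuller document: it prints both sets of figures, and they conflict.

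**Conclusion.** The point holds as a contradiction within the plan. The stated power and sample size belong to a design that differs in number of centres, step spacing and duration from the one described, and they have not been shown for the latter. If the sample size really is 1800, power for the described design is at or below the 80% line on most of the ICC range: 79-84% at best with equal centres, and 56-62% on the least favourable reading of the register year. If the 18 institutions enrol at the stated rates, power averages 83-93% for the mix and rates tried, and it is then the figure of 1800 that is wrong.

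The mismatch is certain, because it stands in the text. The power figures depend on assumed values for the ICC, its decay over time, the sizes of the 18 institutions and their spread over the waves. A clear shortfall has not been shown.

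**What to change.** 1. Reconcile the number of centres, the step spacing and the duration across the sections on randomisation, data analysis and power.
2. Recompute power for the 18 institutions, using each one's register intake, the realised wave allocation, 3-month steps and 16 months (or whichever calendar is confirmed). Use a method for unequal cluster sizes, and take the ICC and the step-to-step correlation from the register year.
3. State whether the register year is in addition to the 1800.
4. Replace the present power statement and planned number with the resulting power, expected number and detectable difference, and give the ICC in the text.

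The cost is a short calculation from national register data that the plan already intends to use. No extra patients are needed. The restated power may be higher or lower than 80%.
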